### Follow-up

Postoperative physiotherapy control visits will take place at 6, 12, 24 and 52 weeks after the procedure. The physiotherapy control visits will be managed by a senior physiotherapist who will be blinded to the allocation group. During the visits, knee ROM and isometric flexion/extension strength will be measured. The isometric extension and flexion strength will be measured with an SBS-KW-300SLIM scale. In addition, the PROMs (KOOS and BPI) will be collected during the research related control visits by the senior physiotherapist at previously defined time points (Table 2).

Postoperative physiotherapy sessions will be provided by physiotherapists who will not otherwise be involved in the study. Physiotherapy control visits and rehabilitation guidance sessions with the treating physiotherapist will take place at 1, 4, 6, 8, 12 and 24 weeks. The physiotherapy protocol will last for 24 weeks. Protocols 1 and 2 are presented in the supplementary material.

Healing of the osteotomy site will be evaluated with plain radiograph examination at 6 and 12 weeks after the procedure. The radiographs will be evaluated by an experienced radiologist and the operating surgeons. Physician visits will be at 6 and 12 weeks. Knee scores and isometric flexion/extension strength will be assessed preoperatively and at 12 and 52 weeks postoperatively.

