## Materials and methods

In this is prospective, randomised, controlled, single-blinded, single centre trial, we compare an accelerated rehabilitation protocol with a typical conservative rehabilitation protocol after DTTO (Fig 1 and Table 1). The trial will be reported in accordance with the Consolidated Standards of Reporting Trials (CONSORT) guidelines.

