### Randomisation

Patients will be randomised using a pre-trial random number matrix in block allocation fashion in varying block. We have two stratification factors. First is age (under 20 and 20–35 years) since age has been shown to associate with the main outcome measure. Another stratification factor will be history of the patellar dislocation i.e. group 1- history with at least 1 documented patellar dislocation and group 2-history with no documented patellar dislocation.

Randomisation will be performed using an online randomisation platform (Redcap). After informed written consent has been received and the intervention in the OR performed, the patients will be randomly allocated for rehabilitation. The physician responsible for the intervention or treatment will not participate in the collection of patient outcomes during the follow-up. Patients are encouraged not to reveal the group to the assessor, so assessor will be blinded. The Patients research data will be concealed to Redcap program until the blinded analysis and two versions of discussions has been agreed. After which the group will be revealed. The research coordinator will monitor the study flow. An independent monitoring committee, which was established during our previous randomised controlled trial, will monitor the study.

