### Rehabilitation

Patients will be randomised in two rehabilitation groups. Patients in both groups will be guided by in-ward physiotherapists and will be given written physiotherapy guidelines for both instructed physiotherapy and self-guided exercises. After discharge from the hospital, patients will be referred to physiotherapy for further guidance. Both groups will start preliminary exercises from the first postoperative day to reduce oedema in the operated lower limb. For the detailed rehabilitation guidelines, please see Table 2.

**Table 2 pone.0304075.t002:** The rehabilitation guidelines.

Elements of physical therapy	Group 1 Accelerated rehabilitation	Group 2 Conservative rehabilitation
Antioedema knee, calf, leg	Day 1	Day 1
Knee brace, ROM limitations	No	6 weeks
Weight-bearing limitations	No, crutches are recommended for 4 weeks.	4 weeks limb weight, followed by half body weight till week 6
Active exercises. Functional exercises.	1 week	8 weeks
Active dynamic strengthening exercises.	5 weeks	8 weeks
Closed chain exercises for muscle strengthening.	8 weeks	8 weeks
Muscle endurance and neuromuscular control, progress strengthening exercises, jogging	12 weeks	12 weeks

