### Interim analysis

The external trial board will execute the interim analysis after half of the patients have been recruited. The analysis will focus on the number of adverse events and the trial board, based on the results of the analysis, will give a recommendation as to whether the trial should continue. If complications rate in accelerated rehabilitation group is remarkably increased in that phase, the study is discarded. Adverse events and serious adverse events will be reported according to the recommendations given by the Consort Group. They will be reported as complications in the final analysis.

Adverse event is defined as follows:

➢ Superficial infection➢ Persisting pain, complex regional pain syndrome or other reasons that can be cured on an ambulatory basis.

Serious adverse event is defined as follows:

➢ Deep infection: Any infection with known bacterial source that calls for re-operation➢ Implant failure leading to displacement of the osteotomy➢ Non-union at 12 weeks control visit

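### Operating surgeons read the healing radiographs although treating physicians are said to be kept out of outcome collection; blinding of the ROM assessor is also thinly protected

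*Protocol article*

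**What the plan says.** The trial is described under Materials and methods as a "prospective, randomised, controlled, single-blinded, single centre trial". Randomisation and Follow-up show that the blinded party is the outcome assessor.

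**On physicians and outcomes.** Randomisation: "The physician responsible for the intervention or treatment will not participate in the collection of patient outcomes during the follow-up". Follow-up: "Healing of the osteotomy site will be evaluated with plain radiograph examination at 6 and 12 weeks after the procedure", and then "The radiographs will be evaluated by an experienced radiologist and the operating surgeons". Interim analysis lists "Non-union at 12 weeks control visit" among the serious adverse events and says of adverse and serious adverse events: "They will be reported as complications in the final analysis". The same section makes the number of adverse events the focus of the interim review. It provides for abandoning the study if complications are markedly more frequent in the accelerated arm.

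**On the assessor.** Randomisation: "Patients are encouraged not to reveal the group to the assessor, so assessor will be blinded". Follow-up has a senior physiotherapist, described as blinded, run the measurement visits at 6, 12, 24 and 52 weeks. Table 2 under Rehabilitation gives the conservative arm a brace for 6 weeks and the weight-bearing rule "4 weeks limb weight, followed by half body weight till week 6". The accelerated arm has no brace and no weight-bearing limit, with crutches recommended for 4 weeks. The primary outcome is knee ROM at 12 weeks.

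**The concern.** Judging union on a plain film involves discretion, and the operating surgeons are not stated to be masked. If their reading counts, people involved in treatment help decide a safety outcome. That outcome bears on the secondary hypothesis (similar complication rates) and on whether the trial continues after the interim. With two kinds of reader and no rule on whose reading prevails, the result could also depend on how disagreements happen to be settled.

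The assessor matter is similar but weaker. ROM is read by hand with a goniometer, so knowledge of the arm could shift the reading. Asking patients to keep silent cannot hide a brace or a pair of crutches. Anything learned at week 6 could carry over to week 12, because the same role measures both. Week-6 ROM is itself a secondary outcome and part of the main hypothesis.

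**Working it through.** **Step 1: surgeons and non-union.**
- Randomisation excludes the physician responsible for the intervention or treatment from collecting outcomes.
- Follow-up names the operating surgeons, with a radiologist, as readers of the healing films at 6 and 12 weeks. Masking is stated for neither.
- Interim analysis makes non-union at 12 weeks a serious adverse event and carries such events into the complication count.
- The link from film to non-union is inferred. No sentence says that the radiograph defines non-union, but plain films are the only assessment of healing described, and one of them is taken at week 12.

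Taken together, the surgeons have a part in an outcome from which the Randomisation section excludes them.

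**Step 2: visible differences when the assessor sees patients.**
- Week 6 (first postoperative assessor visit): the conservative arm's brace period and half-body-weight limit are just ending. The accelerated arm has had no brace, and its recommended crutch period ended at week 4.
- Week 12 (primary outcome): no brace or weight limit is prescribed in either arm.

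Any exposure would therefore arise at week 6 and reach the primary outcome only through what the assessor remembers.

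**Step 3: scale on the primary outcome.** The inputs from Power analysis are a difference of 10°, an SD of 20°, 80% power, 5% type I error (taken as two-sided) and 63 per group.

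Reproducing the plan's figure: n = 2 × (1.960 + 0.842)² × 20² / 10² = 62.8, so 63 per group, as stated.

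Standard error of the between-arm difference: 20 × √(2/63) = 3.56°.

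Suppose there is no true effect but readings differ systematically between arms by b degrees. The rejection probability is P(Z > 1.96 − b/3.56) + P(Z < −1.96 − b/3.56). The values of b are assumptions; none is in the document.

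| Assumed b | b / SE | Two-sided type I error |
|---|---|---|
| 0° | 0 | 5.0% |
| 1° | 0.28 | 5.9% |
| 2° | 0.56 | 8.7% |
| 3° | 0.84 | 13.4% |
| 5° | 1.40 | 28.9% |

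The table uses the unadjusted comparison on which the sample size rests. It says nothing about non-union, for which the document gives no expected rate.

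**The case against.** **On the surgeons.** The document never calls them blinded, so reading films breaks no blinding promise. Reviewing 6- and 12-week radiographs is ordinary aftercare, a radiologist reads the same films, and an external board conducts the interim review. The secondary outcome as worded in Materials and methods names failure of fixation and stress fractures but not non-union. All of this is fair, and it limits the point to a conflict over who contributes outcome data. The conflict remains, because non-union enters the complication count through the Interim analysis section, and the external board can only review events as the readers classified them.

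**On the assessor.** Treating physiotherapists are separate from the assessor, data are held concealed until a blinded analysis is agreed, and visit logistics are detail that an article may leave to the full protocol. That answers part of the point. However, the article does state its mechanism, and it presents the assessor's blindness as following from patients' silence alone. Silence does not cover visible equipment.

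**Stronger readings that the document does not support.**
- A reader might infer that blinding of the primary outcome fails. The document does not say that the brace is worn into the week-6 visit, and none is prescribed at week 12.
- A reader might infer that bias must favour the accelerated arm, because the Introduction expresses a belief in more aggressive aftercare. That is the authors' view; it is not attributed to the assessor or the radiologist.
- A reader might take one row of the table, such as 3° and 13.4%, as an estimate. Nothing in the document supports any particular value.

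**Conclusion.** The point holds in two parts of unequal strength. The main part is a contradiction between Randomisation and Follow-up: surgeons not stated to be masked evaluate the films that, by close inference, inform a serious adverse event used at the interim and in the final complication count. The secondary part is that blinding of the ROM assessor is not adequately protected; it is not shown to fail.

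The size of bias on either outcome cannot be estimated from the document. The illustrative range for ROM runs from 5.9% to 28.9% type I error for assumed reading errors of 1° to 5°. It depends entirely on those assumptions and on the planned SD and group size. The planned sample size is unaffected. This should be corrected, chiefly because it bears on a safety outcome and the correction is cheap.

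**What to change.** 1. Reconcile Randomisation and Follow-up. State that healing and non-union for the interim and final analyses are the planned radiologist's reading, made without knowledge of allocation, and that the surgeons' reading serves clinical care only. This also removes the need for a rule on disagreements. The cost is a sentence or two of protocol wording and withholding the arm from a reader who is already planned.

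2. For the 6-week measurement visit, have someone other than the assessor receive and position the patient, and keep brace and crutches out of the assessor's sight. The cost is small visit logistics; neither rehabilitation schedule changes.

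3. Have the assessor record a guess of allocation at weeks 6 and 12, and report it by arm. The cost is one form item. Interpret it with care: correct guesses can reflect a real difference in knee motion as well as a lapse in masking.

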### Power analysis

We defined 10 degrees [10] in knee ROM in the primary end-point as a clinically relevant difference we would not like miss. We estimated a common standard population deviation of 20 degrees for knee ROM in both groups. Based on unadjusted t-test (TrialSize package in R), we need 63 patients per group to have a power of 80% with 5% type I error level. With this age group, the estimate of loss to follow-up rate will be set to 5% and will result in a total of 132 patients participating in the trial.

### Statistical analysis

Study analysis will be done using mixed linear model allowing for repeated measures in longitudinal setting. All continuous variables will be analyses in this fashion. Each outcome variable will be the dependent variable and patient the random factor. Study group and time point will be included as fixed factor. Stratification variables are included as covariates in the analysis. If baseline value for the dependent variable (i.e. ROM) is available, it will be included also as a covariate. Treatment effects at each time point are the estimated marginal means for time point and study group interaction term. Satterthwaite method is used to estimate degrees in freedom in these analyses. No imputation is needed as liner mixed model is used and a full data set will be used in the analyses. Logistic regression is used to analyse binary outcome. Adjusted risk difference at each time point will be reported for complications and reoperations. All analyses will done with RStudio with suitable packages (i.e. *lmer* and *emmean*).

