** Assessments **						
BPII score	x		x	x	x	x
KOOS	x		x	x	x	x
Adverse events		x	x	x	x	x

TT-distalisation–distalisation of tibial tubercle; BPII–Banff Patella Instability Instrument; KOOS–Knee Injury and Osteoarthritis Outcome Score.

The hypothesis of the trial is that the novel accelerated rehabilitation protocol will lead to faster recovery and improved functional outcome at 6, 12 and 24 weeks compared with the conservative rehabilitation protocol. The secondary hypothesis is that the complication rate will be similar for both protocols.

The primary outcome in this study will be knee ROM measured at 12 weeks postoperatively. A total difference regardless of the direction of the movement of 10° in full range of movement will be considered significant. The results will be measured with a long goniometer in a standardised manner. Secondary outcomes will be knee ROM measured at baseline, 6, 24 and 52 weeks postoperatively, the Knee Injury and Osteoarthritis Outcome Score (KOOS) and the Banff Patella Instability Instrument (BPII) score measured at baseline, 6, 12, 24 and 52 weeks, and isometric muscle strength measured at baseline, 12, 24 and 52 weeks postoperatively. Regained isometric muscle strength will be measured during follow-up visits and calculated to a ratio compared with a preoperative value. The number of reoperations and complications (failure of fixation and stress-fractures) will be also reported as secondary outcomes. The KOOS questionnaire is an instrument to assess patients’ opinions about their knees and any associated problems. KOOS consists of 5 subscales: Pain, other Symptoms, Function in daily living, Function in sport and recreation and knee related Quality of life. BPII is also a patient-reported outcome measurement instrument. BPII is, however, more specific for patellofemoral problems.

After enrolment, all the patients visit the study physiotherapist. The baseline scores from ROM, isometric muscle strength, KOOS and BPII are recorded during the visit. Randomisation to the allocation groups will be done after surgery.

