The ROM measurements are taken with a goniometer, with the patient in supine position. The active ROM is measured as the patient moves the knee in a full range of active flexion and extension. ROM is then measured. Passive ROM is measured in the same supine position. The examiner first moves the knee in a full range of flexion and then in a full range of extension. ROM is then measured. Full ROM is 5º-0º-140º. A ROM of 0º-130º is considered adequate.

The knee extension isometric power measurement is performed with the participant in the sitting position. The isometric power is measured with belts-stabilized dynamometer placed in the support pilar of the treatment table and connected to participants ankle with anchor belt placed 5 cm above the ankle.

The measurement is taken with a dynamometer at three different knee angles 5°, 30° and 90°.

KOOS and BPI are taken before the muscle strength and ROM measurements.

Ethical approval has been obtained from the local health authority. Patients recruited and those patients who declined to take part in the trial but joined the follow-up cohort will provide written informed consent. All data will be deidentified and the results will be published at the group level only. Individual patients will not be identifiable.

The trial is registered in Tampere University Hospital medical research ethics committee ([contact]) on 15.11.2022 with registration number R22072.The trial is registered in ClinicalTrials.gov, Identifier: NCT05854056

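### The ROM model's single patient random effect assumes equal variance at every visit, which is doubtful here and can miscalibrate the per-visit intervals, including the primary one at 12 weeks

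*Protocol article*

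**What the plan says.** The primary endpoint is a single visit: "The primary outcome in this study will be knee ROM measured at 12 weeks postoperatively". The remaining ROM visits are secondary: "Secondary outcomes will be knee ROM measured at baseline, 6, 24 and 52 weeks postoperatively".

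Under Statistical analysis, all continuous outcomes go into one longitudinal mixed model. Group and time point are fixed factors and the stratification variables are covariates. On the random part the article says "Each outcome variable will be the dependent variable and patient the random factor". On baseline it says "If baseline value for the dependent variable (i.e. ROM) is available, it will be included also as a covariate". Visit-specific effects are estimated marginal means for the group-by-time interaction, with Satterthwaite degrees of freedom. `lmer` and `emmean` are given as the packages. No residual covariance or visit-specific variance is mentioned.

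Three other places bear on how ROM will vary:

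- The measurement description sets an upper bound: "Full ROM is 5º-0º-140º".
- Table 2 (Rehabilitation), in the row "Knee brace, ROM limitations", gives 6 weeks for the conservative arm and none for the accelerated arm.
- The Power analysis gives the only ROM SD in the document: "We estimated a common standard population deviation of 20 degrees for knee ROM in both groups".

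**The concern.** A patient random intercept with independent residuals implies compound symmetry: the same variance at each visit and the same correlation between every pair of visits. The 12-week standard error is then not estimated from the 12-week spread. It comes from a variance averaged over all the visits in the model.

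The article's own content makes equal variance doubtful. At 6 weeks one arm is just leaving a motion-limiting brace that the other never wore. Later, recovered knees approach an anatomical limit, which should compress the spread. The full range in the article adds up to about 145° (5° + 140°). If the SD were still 20° when mean ROM had reached 130-135°, a normal model would put 23-31% of knees beyond that limit: P(Z > 15/20) = 0.23 and P(Z > 10/20) = 0.31.

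At stake are the p-value and interval for the primary contrast, and also the 6- and 24-week contrasts that the trial hypothesis names. Where the pooled variance is below a visit's own variance, that visit's interval is too narrow. Where it is above, the interval is too wide and power is lost.

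**Working it through.** **Inputs from the article.** Difference 10°, SD 20°, power 80%, type I error 5%, 63 per group (Power analysis); post-operative ROM visits at 6, 12, 24 and 52 weeks.

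**Assumed.** The SDs at 6, 24 and 52 weeks, since the article gives none. The 20° is kept at 12 weeks throughout. Because the model adjusts for baseline and strata, all SDs should be read as residual SDs.

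**Step 1: the plan's own figure.** n per group = 2 × (1.96 + 0.842)² × 20²/10² = 62.8, so 63. This matches the article (power 80.1% by the normal approximation; the exact t-test needs 64 and gives 79.5% at 63). The sample size is not in question.

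**Step 2: the standard error the model uses.** With n per arm and complete, balanced data, the random-intercept fit gives every visit approximately the same standard error for the group difference:

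- model SE = √(2 × V/n), where V is the mean of the visit variances
- correct SE at visit t = √(2 × SD_t²/n)
- ratio r_t = √V / SD_t
- type I error at visit t ≈ 2 × [1 − Φ(1.96 × r_t)]

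**Step 3: one case in full, SDs 25/20/12/8.** V = (625 + 400 + 144 + 64)/4 = 308.25 and √V = 17.56. The ratios are 0.70, 0.88, 1.46 and 2.19. At 12 weeks, 1.96 × 0.878 = 1.72, a two-sided error of 8.5%. In degrees, the model SE is 17.56 × √(2/63) = 3.13 against a correct 20 × √(2/63) = 3.56.

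**Step 4: the range.**

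| Assumed SDs at 6/12/24/52 weeks | √V | Type I error: 6 wk | 12 wk | 24 wk | 52 wk |
|---|---|---|---|---|---|
| 20/20/20/20 | 20.00 | 5.0% | 5.0% | 5.0% | 5.0% |
| 22/20/18/16 | 19.13 | 8.8% | 6.1% | 3.7% | 1.9% |
| 25/20/15/12 | 18.67 | 14.3% | 6.7% | 1.5% | 0.2% |
| 25/20/12/8 | 17.56 | 16.9% | 8.5% | 0.4% | <0.1% |
| 28/20/16/12 | 19.90 | 16.4% | 5.1% | 1.5% | 0.1% |
| 30/20/12/8 | 19.42 | 20.5% | 5.7% | 0.2% | <0.1% |
| 20/20/10/10 | 15.81 | 12.1% | 12.1% | 0.2% | 0.2% |
| 35/20/10/8 | 21.15 | 23.6% | 3.8% | <0.1% | <0.1% |

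**Step 5: simulation check.** With 6000 simulated trials per scenario (63 per arm, within-patient correlation 0.5, no covariates, Satterthwaite degrees of freedom), coverage at 12 weeks was 94.9% for equal SDs, 94.0% for 22/20/18/16, 94.5% for 30/20/12/8, 87.8% for 20/20/10/10 and 96.2% for 35/20/10/8. These agree with the table. With equal SDs and serial correlation of 0.7 between adjacent visits, coverage stayed at about 95% at all visits. With complete data, then, unequal variance drives the result, not the correlation pattern.

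**Step 6: if baseline were also kept as a response row.** With SD 8 assumed at baseline and 25/20/12/8 afterwards, V = (64 + 1233)/5 = 259.4, √V = 16.11, ratio 0.805, and the 12-week type I error is about 11.4%.

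**The case against.** The strongest reply is that the article cannot show that the variances differ. It gives one SD, for one endpoint, and a random-intercept model is a legitimate choice when variances are equal. That stands. A reader might infer that the intervals are wrong at all four visits and that the primary p-value is necessarily too small. The documents do not support this. Twelve weeks lies between the early and late extremes, so its variance can equal the average (28/20/16/12 gives 5.1%) or fall below it (35/20/10/8 gives 3.8%, slightly conservative).

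The wide spread at 6 weeks is likewise an inference from the brace schedule. Table 2 says nothing about spread.

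A reader might also infer that baseline is modelled both as a response and as a covariate, because it appears among the secondary outcome measurements. That list can equally be a measurement schedule, and the analysis section assigns baseline only a covariate role. Step 6 is a possible reading, not a stated plan.

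Last, covariance structure is often left to a SAP, and one may exist. This carries less weight. The article does not merely stay silent: it names the random factor and the function, and an `lmer` fit with a patient intercept has no visit-specific residual variances. The phrase about suitable packages does not alter the stated random structure.

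**Conclusion.** The point holds in conditional form. The stated model rests every visit's standard error on a pooled variance, and the ROM ceiling and one-arm brace give good reason to doubt that the visit variances are equal.

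In every falling-SD scenario tried, the 6-week interval is too narrow (type I error about 9-24%) and the 24- and 52-week intervals are too wide (under 4%). The primary 12-week contrast runs from about 4% to 12%: too liberal, about right or slightly conservative, depending on how its variance compares with the average. Equal SDs give the nominal 5%.

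These figures assume complete data, the same SD in both arms at a given visit, and visit SDs of which only the 20° comes from the article. With complete data the estimated differences themselves are not biased; only standard errors, intervals and p-values are affected. Confidence is high about the mechanism and low about the exact size. It should be changed, because the validity of the primary test should not hang on an unverified equality that is cheap to drop.

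**What to change.** Replace the random-intercept specification for ROM with a model fitted to the post-operative visits only. Use group × visit, baseline × visit and the stratification factors as fixed effects, and an unstructured within-patient covariance. In R, `mmrm` does this with Satterthwaite degrees of freedom; `nlme::gls` with visit-specific variances and a general correlation is an alternative for the covariance. State in one sentence that baseline enters as a covariate and not as a response row. Name an ANCOVA on the 12-week data, adjusted for baseline and strata, as a check on the primary contrast.

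The cost is a change of wording and of R function. Four visits need 10 covariance parameters (4 variances and 6 correlations) instead of 2, which about 126 evaluable patients can support. The sample size does not change, and if the 12-week SD is 20° the planned power of about 80% is kept.

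### The mixed model appears to use one baseline slope for all visits; a baseline-by-time-point term would protect precision at the secondary visits at very small cost

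*Protocol article*

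**What the plan says.** The protocol article, Statistical analysis, describes one model for all continuous outcomes. Patient is the random factor. "Study group and time point will be included as fixed factor", and the stratification variables are covariates. On the preoperative measurement it states: "If baseline value for the dependent variable (i.e. ROM) is available, it will be included also as a covariate". The effect at each visit is taken from the group-by-time-point interaction, which is the only interaction mentioned.

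The primary outcome is knee ROM at 12 weeks; ROM at 6, 24 and 52 weeks is secondary. The trial hypothesis names 6, 12 and 24 weeks. In the Rehabilitation section, the row "Knee brace, ROM limitations" of Table 2 shows none for the accelerated group and 6 weeks for the conservative group.

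The Power analysis section supplies the only variance figure: "We estimated a common standard population deviation of 20 degrees for knee ROM in both groups". The sample size rests on an unadjusted t-test. No correlation between baseline and any follow-up visit is given, and no preoperative SD.

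**The concern.** A single baseline main effect makes the preoperative value predict the outcome with the same slope at every visit. That is a doubtful restriction here. Week 6 follows closely on an osteotomy and falls at the end of bracing in one arm, while week 52 comes long after the 24-week physiotherapy protocol has ended. Preoperative ROM could well relate differently to these two measurements.

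If the slopes differ, the fitted common slope is roughly their average and is wrong at the outer visits. Baseline variation that could have been removed then stays in the error of the visit-specific contrast. Since the plan reports an effect at every visit, and week 6 is part of the hypothesis, the precision of the secondary visits is at stake. Validity is not.

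**Working it through.** **The plan's own figure.** Difference 10 degrees ("We defined 10 degrees [10] in knee ROM in the primary end-point as a clinically relevant difference"), SD 20, two-sided 5%, power 80%:

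n per group = 2 × (1.960 + 0.842)² × 20² / 10² = 62.8, rounded up to 63.

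This matches "we need 63 patients per group to have a power of 80% with 5% type I error level" (power 80.1% by the normal approximation). For 5% loss, 126/0.95 = 132.6, against a stated 132; the difference has no bearing on this point.

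**Formulas.** Take complete data and a random intercept per patient. Let r_v be the correlation of baseline with visit v, and b_v = r_v × SD_v / SD_x the slope at that visit. Baseline does not vary over time, so the common slope b is the mean of the four b_v. Then:

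- excess variance of the contrast at visit v, one slope against visit-specific slopes = (b − b_v)² × SD_x² / [SD_v² × (1 − r_v²)]
- shift in the estimate for a one-standard-error baseline imbalance = |b − b_v| × SD_x × √(2/63)

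These are two views of one quantity: the excess variance is the variance of that shift. They must not be added as separate harms.

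**Excess variance.** All correlations are assumed. SD is 20 at baseline and every visit unless stated.

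| r at weeks 6 / 12 / 24 / 52 | b | wk 6 | wk 12 | wk 24 | wk 52 |
|---|---|---|---|---|---|
| 0.4 throughout | 0.400 | 0% | 0% | 0% | 0% |
| 0.30 / 0.35 / 0.40 / 0.45 | 0.375 | 0.6% | 0.1% | 0.1% | 0.7% |
| 0.2 / 0.3 / 0.4 / 0.5 | 0.350 | 2.3% | 0.3% | 0.3% | 3.0% |
| 0.5 / 0.4 / 0.3 / 0.2 | 0.350 | 3.0% | 0.3% | 0.3% | 2.3% |
| 0.1 / 0.3 / 0.4 / 0.6 | 0.350 | 6.3% | 0.3% | 0.3% | 9.8% |
| 0.1 / 0.3 / 0.5 / 0.7 | 0.400 | 9.1% | 1.1% | 1.3% | 17.6% |
| 0.1 / 0.2 / 0.5 / 0.7 | 0.375 | 7.6% | 3.2% | 2.1% | 20.7% |
| 0.1 / 0.3 / 0.4 / 0.6, with SD 25 / 20 / 15 / 10 and baseline SD 10 | 0.5125 | 1.1% | 0.2% | 0.4% | 1.2% |

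Example, fifth row: week 6 is (0.35 − 0.10)² / (1 − 0.01) = 0.0625/0.99 = 6.3%; week 52 is (0.35 − 0.60)² / (1 − 0.36) = 0.0625/0.64 = 9.8%. A deliberately extreme pattern (0 / 0.2 / 0.5 / 0.8) gives 14%, 3.2%, 2.1% and 50%.

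**Shift in degrees.** With √(2/63) = 0.178, rows five and seven give, at week 6, 0.25 × 20 × 0.178 = 0.9 and 0.275 × 20 × 0.178 = 1.0. At week 52 they give 0.25 × 20 × 0.178 = 0.9 and 0.325 × 20 × 0.178 = 1.2, in the opposite direction. With the unequal SDs of the last row the shift is 0.2625 × 10 × 0.178 = 0.5 at week 6 and 0.0875 × 10 × 0.178 = 0.2 at week 52. All are small against 10 degrees.

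**Power for 10 degrees at 63 per group, one slope against visit-specific slopes.**

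- Week 12: 86.5 v 86.5% (flat), 85.0 v 85.0% (0.30 to 0.45), 83.6 v 83.7% (0.2 to 0.5), 83.3 v 83.7% (0.1/0.3/0.5/0.7), 80.5 v 81.7% (extreme).
- Under 0.1/0.3/0.5/0.7: week 6, 77.1 v 80.5%; week 52, 95.2 v 97.6%.

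**Bias and cost.** A simulation of 20,000 trials (63 per arm, correlation 0.5 between follow-up visits) found an average error of at most 0.05 degrees with one slope. With equal slopes, the extra terms raised the standard error by 0.15% to 0.23%, or about 0.3% to 0.5% in variance. In the mild and moderate rising patterns, visit-specific slopes were about 0.1% worse in standard error at week 12.

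**The case against.** The strongest reply is that nothing here is wrong. A common baseline slope is a standard and valid choice, and the estimates are unbiased. The section is also a condensed description: its sentence on fixed factors omits even the group-by-time interaction, which appears only later, so the absence of a baseline-by-time term is weak evidence that it is excluded. An analysis plan that is not shown may contain it. All of this stands, and it limits the point to a suggestion.

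A reader might go further and infer that baseline is over-corrected at week 6 and under-corrected at week 52. The documents do not support this as a fact. It needs a slope that rises over time, and no such figure is given. Flat slopes remove the pattern and falling ones reverse it. Even rising correlations are not enough, because the slope also depends on the SDs: with SDs 25, 20, 15, 10, baseline SD 10 and correlations 0.2, 0.3, 0.4, 0.5, the slopes are 0.5, 0.6, 0.6, 0.5 with mean 0.55, so week 52 is over-corrected too.

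It is also fair to object that the larger losses fall on secondary visits, and that the largest, at week 52, lies outside the hypothesis. Of the visits in the hypothesis, only week 6 loses more than about 3% in any pattern tried. Strength needs separate treatment: it has no week-6 measurement and is to be expressed as a ratio to the preoperative value, so the week-6 figures do not carry over. No figures are available for KOOS or BPII.

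What survives is the asymmetry: a very small cost if the slopes are equal, against a moderate gain at weeks 6 and 52 if they differ steeply.

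**Conclusion.** The point holds as a low-cost improvement in efficiency. Read plainly, the model has one baseline slope but visit-specific treatment effects. If the slopes rise steeply (correlation 0.1 at week 6 to 0.6 or 0.7 at week 52, equal SDs of 20), the variance is about 6% to 9% larger than necessary at week 6 and 10% to 21% larger at week 52. With milder, falling or differently scaled slopes the loss at either visit is about 3% or less (1.5% or less in standard error), and with equal slopes it is nil. At the primary week-12 visit it is about 0% to 3%, and power stays above 80% in every pattern evaluated.

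These sizes rest on assumed correlations and SDs, complete data and a random-intercept reading of the model. Two stronger conclusions are not supported: that the planned estimates are biased, and that the primary comparison is underpowered because of this choice.

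**What to change.** Pre-specify a baseline-by-time-point interaction for each continuous outcome that has a baseline covariate and repeated follow-up visits, and take the group contrast at each visit from that model. If the analysis plan already includes the term, it is enough to confirm this. For strength, the term applies only if a preoperative value is actually used as a covariate alongside the ratio.

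The cost is three extra parameters with four follow-up visits (two with three) and some 0.3% to 0.5% in variance if the slopes are in fact equal. No further data are needed and the sample size is unaffected. The choice should be fixed before allocation is revealed.
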